**Objective:**

This study aims to elicit cognitive readiness and therapeutic engagement by adding tACS to each CBTp session in individuals with schizophrenia taking their usual medication, to evaluate the possible improvement of the level of functioning, and to determine if the response to intervention is gender specific.

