### Statistical Considerations: Sample Size

This is a pilot randomized study with 28 participants (14 per arm). The primary goals are to evaluate recruitment feasibility, acceptability, and safety, and to produce unbiased estimates of the standard deviation and preliminary effect sizes of the primary outcome to inform sample-size calculation for a future definitive trial [31]. A target of 28 participants is consistent with common pilot rules-of-thumb (approximately 12-20 per arm) and provides sufficient precision to estimate recruitment and retention rates and the outcome variance. This pilot is not powered for hypothesis testing of efficacy (with n=14 per group, the minimal detectable standardized effect is large, ~*d*=1.1); outcome analyses will therefore be descriptive and will report effect estimates with 95% CIs as inputs for future sample-size calculations. To allow for expected attrition (approximately 15%-20%), we will recruit up to 33-40 participants. The generalizability of our findings is limited by the small sample size (n=28) and recruitment from a single treatment site. Patients in this cohort may differ from the broader schizophrenia population with respect to illness chronicity, symptom severity, comorbid psychiatric or medical conditions, and sociodemographic characteristics. In addition, the specialized treatment context may not reflect the experiences of individuals receiving care in community or primary care settings, where clinical resources and treatment approaches may vary. These factors restrict the extent to which the present results can be applied to other patient populations. Replication in larger, multisite, and more heterogeneous cohorts will be essential to establish the robustness and external validity of the findings.

The statistical analysis plan will use SPSS (version 29, IBM Corp) for the main tests, including effect size (Cohen *d*) and a 95% CI: repeated measures, mixed design analysis of variance, and *t* tests for two-group comparisons. Sex and gender differences will be examined using regression models that include biological sex, BSRI masculinity and femininity scores, and their interaction terms, with exploratory subgroup analyses based on BSRI classifications.

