PETiT is a self-administered scale, which is user-friendly and sensitive to changes associated with treatment over time [26]. Consisting of 30 items, it assesses the respondent’s health over the last week and provides 1 of 3 responses (“often,” “sometimes,” or “never”). The scale assesses 2 highly relevant domains for schizophrenia: adherence-related attitude (includes 6 items reflecting adherence and feelings toward medication) and psychosocial functioning (24 items describing patient characteristics such as clarity, energy, concentration, functioning, sex drive, and memory). The PETiT total score ranges from 0 to 60, with higher scores indicating better patient health-related quality of life. [Time frame: PETiT will be performed at visit 2, baseline (week 1); visit 4, end of intervention (week 17); visit 5, follow-up 1 (week 21); and visit 6, follow-up 2 (week 29).]

The Working Alliance Inventory—Short Revised (WAI-SR), both forms, that is, for client and therapist, measures 3 critical aspects of the therapeutic alliance: agreement on the tasks of therapy, agreement on the goals of therapy, and development of an affective bond [40]. The 12 items are rated on a 5-point Likert scale ranging from “1=never” to “5=always.” The scores range from 5 to 20, with higher scores indicating a better therapeutic alliance. Completing the WAI-SR takes about 5 minutes. [Time frame: WAI-SR will be tested at visit 3, midterm through intervention (week 9); and visit 4, end of intervention (week 17).]

The BSRI is a psychological tool used to measure an individual’s perception of their own masculinity and femininity, and it is used to research gender roles, with the understanding that individuals can express both masculine and feminine traits. The interview has 12 items, with scores on a 1 (never or almost never true) to 7 (always or always true) scale, with an average calculated for masculine and feminine traits, and then categorizes them as masculine, feminine, androgynous, or undifferentiated based on those scores. Each item is assigned a category as follows: M for masculine, F for feminine, and N for neutral. [Time frame: BSRI is performed at visit 1, screening (week 0).]

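### The sex/gender regression, as worded, has six or seven terms for about 28 participants but no arm interaction, so it cannot estimate whether the effect of tACS differs by sex or gender role

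*Protocol article*

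**What the plan says.** The final paragraph of *Statistical Considerations: Sample Size* (Protocol article) states: "Sex and gender differences will be examined using regression models that include biological sex, BSRI masculinity and femininity scores, and their interaction terms". The same sentence then adds a second layer, by gender-role class: "with exploratory subgroup analyses based on BSRI classifications". The BSRI entry under *Secondary Outcome Measures* describes masculinity and femininity averages for each respondent and then "categorizes them as masculine, feminine, androgynous, or undifferentiated based on those scores", which gives four classes.

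The question these analyses serve is in the abstract's *Objective*: "to determine if the response to intervention is gender specific". The *Objectives* section repeats it as the third secondary objective, under the same verb, *determine*.

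The size is fixed in the sample-size section: "This is a pilot randomized study with 28 participants (14 per arm"). The section adds "To allow for expected attrition (approximately 15%-20%), we will recruit up to 33-40 participants". It concedes that "with n=14 per group, the minimal detectable standardized effect is large" (d about 1.1) and concludes that "outcome analyses will therefore be descriptive and will report effect estimates with 95% CIs as inputs for future sample-size calculations".

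**The concern.** Whether a randomised treatment works differently by sex or gender role is a question about effect modification. It needs a term that compares the arm difference across levels of the moderator. The sentence on sex and gender lists three predictors and the interactions between them, and arm is not one of them. Both arms receive CBTp, so a model without arm can show only that, say, higher femininity scores go with more change under CBTp, whether or not stimulation was given.

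The model is also large for the sample. Its degrees of freedom go on products among sex, masculinity and femininity, which the objective does not ask about. A gender finding from this model could be reported as an answer to the third secondary objective when it is not one. A real difference in the effect of tACS between men and women would have no coefficient of its own.

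**Working it through.** **Inputs from the protocol.** 28 participants, 14 per arm; 33-40 recruited, with 15%-20% attrition expected; three predictors plus interactions; four BSRI classes; d about 1.1 as the smallest detectable effect.

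**Assumptions.** Two-sided 5% and 80% power (not stated, but they reproduce the 1.1); 7 people in each arm-by-sex cell. Randomisation is stratified by sex, which balances arms within sex but does not fix the proportion of men and women, so unequal splits are shown too.

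**1. The plan's own figure.** SE of a two-arm difference in SD units = sqrt(2/14) = 0.378, with 26 df. Smallest detectable effect = (t0.975 + t0.80) x SE = (2.056 + 0.856) x 0.378 = 1.10. This agrees with the protocol.

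**2. Terms in the stated model.** Three main effects + three two-way products = 6; adding the three-way product gives 7. Residual df = n - terms - 1.

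| n analysed | 6 terms: df, people per term | 7 terms: df, people per term |
|---|---|---|
| 28 | 21, 4.7 | 20, 4.0 |
| 32 (40 recruited, 20% lost) | 25, 5.3 | 24, 4.6 |
| 40 (no loss) | 33, 6.7 | 32, 5.7 |

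At n = 28 with 7 terms, a single coefficient reaches 80% power only at f-squared of about 0.31, a partial R-squared of 0.31/1.31 = 0.24.

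**3. Arm under other readings of the sentence.** Crossing arm fully with the 7-term model gives 15 terms and 28 - 15 - 1 = 12 df. Reading the interactions as arm by each moderator gives arm + 3 moderators + 3 interactions = 7 terms and 20 df. The sentence states neither.

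**4. Precision of the contrast the objective needs (arm by sex).** The interaction is a difference of two differences over four cells: SE = sqrt(4/7) = 0.756 SD, exactly twice the 0.378 in step 1, with 28 - 4 = 24 df.
- 95% CI half-width = 2.064 x 0.756 = 1.56 SD.
- Smallest detectable value = (2.064 + 0.857) x 0.756 = 2.21 SD.
- With a 9/5 sex split in each arm: half-width 1.63 SD, detectable 2.3 SD. With 10/4: 1.73 SD and 2.4 SD.

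**5. Four-class subgroups.** 28 / (4 classes x 2 arms) = 3.5 people per class per arm. A comparison of 4 against 3 has a CI half-width of 2.571 x sqrt(1/4 + 1/3) = 1.96 SD. If the four classes were equally likely (an assumption), the chance that at least one of the eight cells holds one person or none is 0.62.

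**6. The replacement model.** Arm + one moderator + their interaction = 3 terms, with 24 df and 28/3 = 9.3 people per term.

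**The case against.** Most of the imprecision is admitted. The same section calls the pilot unpowered for efficacy, makes outcome analyses descriptive with 95% CIs, and labels the BSRI class analyses exploratory. Exact model specification is commonly left to an SAP, the text says *models* in the plural, and the three-way term is never stated. This stands as far as it goes. However, the power caveat and the figure of 1.1 concern the two-arm comparison, so nothing tells the reader that the gender contrast has twice the standard error. The exploratory label is attached to the class subgroups and not to the regression. The model's terms are written down, and arm is not one of them.

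A reader might go further and infer that any gender-specific finding from this plan would be mostly chance. The documents do not support that. The share of significant results that are false is 0.05(1 - prior) / [0.05(1 - prior) + power x prior], and the protocol gives neither a prior nor an effect size. Across assumed priors of 0.1 to 0.5 and f-squared of 0.02 to 0.35, the share runs from 80% down to 6%. It exceeds half only for small effects with priors of about 0.3 or lower.

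Nor is the chance of some p < 0.05 a small-sample defect. In simulation with no true association (balanced sex, normal scores) it is about 24%-25% per outcome at n = 28 and 28% at n = 100. That is ordinary multiplicity over six or seven tests. Three separate moderator-by-arm models give 31% if every term is counted, and about 15% if only the three interactions are. The replacement model is therefore justified because it answers the question, not because it controls false positives.

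Treating 28 as a strict ceiling would also be wrong, since up to 40 may be recruited. Step 2 shows that this changes little.

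**Conclusion.** The point holds as a mismatch between model and objective, made worse by imprecision. The stated regression spends six or seven terms on about 28 people (20-21 residual df) and, on its natural reading, contains no coefficient for whether the arm difference varies by sex or gender role. The third secondary objective cannot be met from it. The simplest contrast that would address the objective can only be estimated to within about 1.6 SD either side, with about 2.2 SD detectable, so *determine* promises more than the trial can give. These figures assume 7 per arm-by-sex cell, two-sided 5% and 80% power; uneven sex splits make them worse.

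The four-class subgroups are very thin but already labelled exploratory, and they are not a fault if kept to description. The protocol contains no numerical error here: its 1.1 is reproduced. The change is worth making because it is cheap and the objective is otherwise left without an analysis.

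**What to change.** - In *Statistical Considerations: Sample Size*, replace the products among sex, masculinity and femininity with three separate models per outcome. Each contains arm, one moderator (sex, continuous masculinity score or continuous femininity score) and the single arm-by-moderator interaction. Report the interaction as an estimate with 95% CI and make no significance claim.
- In the abstract's *Objective* and in the third secondary objective, change *determine* to *estimate (exploratory)*, in line with the descriptive stance of the sample-size section.
- State the expected precision: with an assumed 7 per arm-by-sex cell, CI half-width about 1.6 SD and smallest detectable interaction about 2.2 SD (two-sided 5%, 80% power).
- Keep the four BSRI classes as descriptive tables only.

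The cost is wording in the protocol and SAP. Masculinity and femininity will no longer be adjusted for each other, and their product is not examined. The change does not remove multiplicity across three interactions and several outcomes, and it does not make the interaction precise.

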### Statistical Outcomes

#### Primary Outcome Measures

EEG gamma oscillations are fast neural rhythms linked to higher-order cognitive functions (attention, working memory, executive control, and consciousness). In the prefrontal cortex, gamma EEG activity is associated with working memory maintenance, cognitive flexibility, top-down attention control, and integrating information across cortical areas. Altered prefrontal gamma observed in schizophrenia. EEG measurement of gamma activity in the prefrontal cortex refers to detecting brain oscillations in the gamma frequency band (typically 30-100 Hz, often subdivided into low gamma: 30-50 Hz, and high gamma: 60-100 Hz) from scalp electrodes positioned over prefrontal areas. In a within-subject design, we will compare gamma power across time windows (pre- and postintervention). In a between-subject design, we use mixed models or *t* tests on summary metrics (mean power in time×freq window).

PANSS is a standardized clinical interview that rates the presence and severity of positive and negative symptoms and general psychopathology for people with schizophrenia within the past week [32]. The scale consists of 30 items: 7 positive, 7 negative, and 16 general psychopathology symptoms. The symptom severity for each item is rated according to a 7-point scale (1=absent to 7=extreme) to best describe the symptom’s presentation. The clinical interview takes approximately 45 minutes. The patient is rated from 1 to 7 on 30 different symptoms based on the discussion and reports of family members or primary care hospital workers. As 1 is the lowest score for each item, a patient cannot score lower than 30 for the total PANSS score. Scores are often given separately for positive items, negative items, and general psychopathology. [Time frame: PANSS will be applied at visit 1, screening (week 0); visit 4, end of intervention (week 17); visit 5, follow-up 1 (week 21); and visit 6, follow-up 2 (week 29).]

The NSA-16 assesses the presence, severity, and range of negative symptoms associated with schizophrenia [33]. For rapid clinical assessment or screening of patients for negative symptoms, the NSA-4 was developed as a simplified version, retaining only 4 of the 16 items: restricted speech quantity, reduced emotion, reduced social drive, and reduced interests. Each of the 4 items and the overall global negative symptoms is rated on a 1- to 6-point scale, where “1” represents no reduction from normal behaviors associated with the item and “6” represents a severe reduction in or absence of the behavior, with markedly impaired functionality. With respect to overall accuracy and predictive validity, the NSA-4 is comparable to the NSA-16. [Time frame: NSA-16 will be applied at visit 2, baseline (week 1); visit 4, end of intervention (week 17); visit 5, follow-up 1 (week 21); and visit 6, follow-up 2 (week 29).]

The CFS assesses cognitive flexibility as a factor that facilitates the individual’s adaptability toward events [34]. Cognitive flexibility refers to a person’s awareness of the existence of different communication styles in every situation, as well as their willingness and self-efficacy to employ these styles. The scale has 12 items pertaining to the 3 elements of cognitive flexibility: a person’s awareness of alternative communicative styles, willingness to be communicatively flexible, and self-efficacy in being communicatively flexible. The scale uses a 6-point Likert-type scale for each item (with 6 as “strongly agree,” 5 as “agree,” 4 as “slightly agree,” 3 as “slightly disagree,” 2 as “disagree,” and 1 as “strongly disagree”). The total score was used to calculate a global score ranging from 12 to 72, with questions 2, 9, 11, and 12 being reverse-coded. A higher score indicates higher cognitive flexibility. [Time frame: CFS will be applied at visit 2, baseline (week 1); visit 3, midpoint of intervention (week 9); visit 4, end of intervention (week 17); visit 5, follow-up 1 (week 21); and visit 6, follow-up 2 (week 29).]

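### The between-arm EEG comparison names no baseline-adjusted analysis, although week-0 gamma power is collected; ANCOVA would give a narrower confidence interval at no cost

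*Protocol article*

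**What the plan says.** The EEG paragraph under Primary Outcome Measures in the protocol article sets out two comparisons. The first is within participants: "In a within-subject design, we will compare gamma power across time windows (pre- and postintervention"). The second is between arms: "In a between-subject design, we use mixed models or" t tests "on summary metrics (mean power in time×freq window"). The paragraph does not say which of the two methods applies, whether the summary is the week-17 value or a change, or whether baseline gamma power enters the model.

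Statistical Considerations: Sample Size lists the main tests as repeated measures, mixed design ANOVA and t tests for two groups, with Cohen d and a 95% CI. No baseline covariate is named for the arm comparison. The same section gives the size ("This is a pilot randomized study with 28 participants (14 per arm")) and the purpose: "outcome analyses will therefore be descriptive and will report effect estimates with 95% CIs as inputs for future sample-size calculations".

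Table 2 schedules EEG at visit 1 (week 0) and visit 4 (week 17) only. The Abstract speaks of the primary measures at the follow-ups as well, but Table 2 shows no EEG there; this point follows Table 2. Under CBTp Intervention, both arms receive CBTp.

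**The concern.** The pilot exists to deliver effect estimates and their uncertainty for a later trial, so precision is its product. Each participant will have one gamma value before treatment and one after. With two such values in a randomised comparison, adjusting the second for the first gives an arm difference at least as precise as either alternative, apart from a small cost in degrees of freedom and chance imbalance. The methods the article names do not clearly do this. One can leave the baseline out; the other subtracts it in full, whatever its correlation with the week-17 value.

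The pre/post comparison raises a separate question of reading. The first primary objective expects EEG activity to rise in both groups because of CBTp, and more with active tACS. No arm goes without CBTp, so a rise within participants could come from CBTp, from time, from repeat recording or, in the active arm, from tACS. The article does not label this comparison as secondary to the between-arm one.

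**Working it through.** **Inputs.** n = 14 per arm (Sample Size section). EEG at weeks 0 and 17 (Table 2). 95% CI, hence two-sided alpha 0.05 (Sample Size section). Assumed, because the article does not give them: 80% power for the detectable effect; correlation r between week-0 and week-17 gamma power; the same SD at both times and in both arms. Results are in units of that SD.

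**The protocol's own figure.** The article says: "This pilot is not powered for hypothesis testing of efficacy (with n=14 per group, the minimal detectable standardized effect is large", about d = 1.1. A two-sample t test with 14 per arm, 26 df, two-sided alpha 0.05 and 80% power (noncentral t) gives a detectable d of 1.10. The figure is right, and it matches an unadjusted two-group t test.

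**Variance of the arm difference.** It is f × 2/14, with
- week-17 t test: f = 1, 26 df
- change score: f = 2(1 − r), 26 df
- ANCOVA on week-0 power: f = 1 − r², 25 df

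With two time points, the group-by-time term of a mixed ANOVA is the change-score comparison.

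**95% CI half-width** = t(0.975, df) × √(2f/14), where t is 2.056 for 26 df and 2.060 for 25 df.
- Week-17 t test, any r: 2.056 × √(2/14) = 2.056 × 0.378 = 0.78
- ANCOVA, r = 0.5: 2.060 × √(0.75 × 2/14) = 2.060 × 0.327 = 0.67
- ANCOVA, r = 0.7: 2.060 × √(0.51 × 2/14) = 2.060 × 0.270 = 0.56
- Change score, r = 0.7: 2.056 × √(0.60 × 2/14) = 2.056 × 0.293 = 0.60

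| r (assumed) | Week-17 t test | Change score | ANCOVA |
|---|---|---|---|
| 0.3 | 0.78 | 0.92 | 0.74 |
| 0.5 | 0.78 | 0.78 | 0.67 |
| 0.6 | 0.78 | 0.69 | 0.62 |
| 0.7 | 0.78 | 0.60 | 0.56 |
| 0.8 | 0.78 | 0.49 | 0.47 |

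ANCOVA is narrowest in every row. Below r = 0.5 the change score is wider than the week-17 test.

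**Variance saving from ANCOVA.** Against the week-17 test it is r²: 25% at r = 0.5 and 49% at r = 0.7. Against the change score it is 1 − (1 − r²)/(2(1 − r)) = (1 − r)/2: 25% at r = 0.5 and 15% at r = 0.7.

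**A small cost left out of the table.** Chance imbalance in the baseline raises the ANCOVA variance on average by 1/(28 − 4) = 1/24, about 4%, for a normally distributed covariate. The half-width grows by √1.042 = 1.02, for example from 0.56 to 0.57 at r = 0.7. The ordering in the table does not change.

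**Within-participant comparison.** Suppose there is no tACS effect and both arms rise by 0.5 SD (assumed). At r = 0.5 the SD of change is √(2 × 0.5) = 1, so the noncentrality of a paired t test in one arm is 0.5 × √14 = 1.87, and it is significant with probability 0.41. Exactly one of the two arms is then significant with probability 2 × 0.41 × 0.59 = 0.48. Contrasting within-arm results could thus suggest a difference between arms about half the time with none present.

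**The case against.** The strongest reply is that this is a journal article, the analysis plan is not shown, and the choice of covariates is commonly left to that plan. The article makes no false statement about the EEG analysis. A mixed model can be specified to adjust for baseline, and a summary metric could be a change. Outcome analyses are declared descriptive, so no EEG test decides anything.

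Much of this stands. It does not remove the point, because the article does state what the main tests will be, and none of those named clearly adjusts for the baseline. The descriptive purpose makes CI width the right yardstick, and that is where the gain lies.

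Several stronger readings are tempting, and the article does not support them:
- That the EEG analysis is only an uncontrolled pre/post contrast. A between-arm comparison follows in the next sentence.
- That gamma will be analysed over 30-100 Hz. That range is a general definition, "often subdivided into low gamma: 30-50 Hz, and high gamma: 60-100 Hz"; it is not given as the analysis window. Fixing the band is detail that may sit in the analysis plan.
- That two sub-bands and two tests give four candidate primary results, chosen after seeing the data. Nothing in the article says so.
- That adjustment is worth a 49% cut in variance, or a fall in the detectable effect from 1.10 to 0.79 SD. Both figures take r = 0.7 and compare with a week-17 t test only. Against the change score at the same r, the variance saving is 15%.

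**Conclusion.** The point holds as a free improvement in precision; it is not an error in the plan. With EEG at two time points, neither a week-17 t test nor the group-by-time term of a mixed ANOVA is the most precise estimate of the arm difference. At 14 per arm and an assumed r of 0.5 to 0.7, ANCOVA gives a 95% CI half-width of about 0.67 to 0.56 SD, against 0.78 SD and 0.78 to 0.60 SD respectively. Against the change score the gain shrinks as r rises: 0.47 against 0.49 SD at r = 0.8. The size rests on the assumed correlation, equal SDs and 14 analysed participants per arm; over r = 0.3 to 0.8 the direction does not change.

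The within-participant change may be reported, but it identifies neither a tACS effect nor a CBTp effect. A reader might infer that the article presents it as evidence of tACS against sham. It does not say that; what it lacks is a label that rules the reading out.

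**What to change.** In the EEG paragraph, replace the open choice of methods with one analysis: the between-arm difference in week-17 prefrontal gamma power, estimated by ANCOVA with week-0 gamma power as covariate, or by an equivalent mixed model that constrains the arms to a common baseline mean. Report that difference with its 95% CI as the EEG effect estimate. State that within-participant pre/post change is descriptive and is not used to infer an effect of tACS or of CBTp. Bring the list of main tests in the Sample Size section into line.

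The cost is wording and one degree of freedom; no visit, recording or participant is added. The stratification factors are not needed as covariates for this gain, and age could not be coded as written, because the strata (18-30, 31-55, >60 years) leave out ages 56 to 60.
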